### Participating Wards

The study will involve 52 psychiatric wards in 52 hospitals in Germany treating patients with severe mental illness, including involuntary treatment. Prerequisites for participation are a written declaration of support by the hospital management and the ward management, the willingness to work with agreements on objectives, and the provision of the cumulative evaluation of the outcomes for research purposes. Wards of forensic psychiatry, child and adolescent psychiatry, and wards where mainly people suffering from dementia are treated are excluded from the trial.

### Recruitment of Wards

Two study centers are planned: One in north-eastern (Berlin) and one in the south-western (Ravensburg) of Germany. Each study center has to recruit and supervise 50% of the wards. Hospitals can participate with more than one ward. A contract will be signed with description of duties of each party. There are no financial incentives for participating hospitals, but continuous support and counseling by a research worker.

### Interventions

In the beginning, a first workshop to assess the present state of clinical practice together with the ward team will be held. This data will be used for matching and randomization of the wards. The possible interventions will be presented to the ward team within a second awareness workshop. The research assistant will support staff to select appropriate interventions. Subsequently, the research assistant will provide advice on how to realize the intervention and will establish action plans with targets and timelines in close collaboration with the ward team. During the implementation process, an interactive counseling will be realized with selected key persons on the ward *via* telephone and email. Key persons will also receive advice on collecting and delivering data. A third workshop will be during the intervention period. At the end of the study period, a fourth visit of the team will be realized by the research worker. The planned timeline is shown in **Figure 1**. The 12 offered and recommended guideline-based interventions are as follows:

Implement a standardized recording of coercive measures and aggressive incidents with the possibility of regular evaluation at ward level.Implement internal standards adapted to the guidelines regarding the indication, initiation, review, documentation, and debriefing of coercive measures, or review existing standards, as appropriate.Hold a monthly team meeting, chaired by the department or ward manager, to analyze data on coercive measures and aggressive incidents and discuss the background.Implement a training plan for all employees with patient contact in de-escalation/aggression management and ensure that all employees receive training at least once every two years.Ensure that any coercive measures restricting or depriving freedom (restraint, seclusion) are accompanied by continuous observation and personal care.Ensure that debriefings after coercive measures with the affected patients take place and are documented.Employ or involve peers on the ward.Create an action plan for the aggression-reducing design of the spatial environment on the ward and review it annually.Introduce a risk assessment with the Brøset Violence Checklist (BVC) or another instrument for all patients at risk according to clinical assessment and make sure that clinical consequences result. For scores above BVC 2, e.g., the patient is contacted for de-escalation within half an hour, usually by at least two persons.During debriefing after a coercive measure, recommend all patients to draw up a joint crisis plan for the prevention of future coercion.Introduce measures to ensure guideline-based pharmacotherapy [based on the guideline with regard to aggressive behavior, but also the disorder-specific other guidelines (“guideline-based treatment of the underlying disease”)], and, e.g., monthly random check or hold regular meetings during roundsIntroduce complex interventions for reducing coercion that can be operationalized into individual modules (e.g., Safewards, Weddinger Model, Six Core Strategies).

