**Figure 1 f1:**
[figure not shown]
SPIRIT flow chart: Timeline and study procedures.

Due to the heterogeneous initial situation of each ward need for action will have to be determined for each ward individually. To this end, research workers and ward managers will jointly evaluate the status of implementation at the first visit. Afterwards, ward staff will discuss and declare their preferred interventions. A set of up to three selected interventions will be the ward’s working focus during the interventions period. However, e.g., implementing a complex intervention such as Safewards is considered as sufficiently demanding to be selected alone. The underlying idea is that it would be unrealistic to fully implement all 12 recommendations within 12 months. Demand this would probably result in a low fidelity to the intervention. In addition, we assume that it makes little sense to require the implementation of elements of the intervention that might be viewed as unfeasible or undesirable by the staff. On the other hand, this means that the intervention will not be fully completed after the study period and cannot have unfolded its full power. Rather, implementation has to be considered as a process over several years, with the study intervention only boosting an initial period. The selection of individually fitting interventions by participating wards means that not all participants will deliver identical interventions. The qualitative interviews are intended to explore, among other things, why interventions are selected and which barriers had arisen during implementation.

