### Standard of Care on Control Wards

The legal requirements (mental health laws, civil code) already require the use of coercion to be limited to a necessary minimum. The participating wards should continue to apply their current strategies to prevent coercion and violence, even if they are randomized into the control group and even if these strategies are also mentioned in the 12 interventions. New structured programs especially with external supervision to reduce coercion and violence further should not be implemented in this phase. However, control wards will be informed about the program and its possibilities and spill-over effects cannot be ruled out. To detect such effects, a second measurement of implementation status and outcomes will take place on the control wards before the beginning of the intervention after the waiting list status.

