### Outcomes

The primary endpoint will be the number of coercive measures per bed and month/year for each ward (intervention wards vs. waiting list wards). This dependent variable includes forced medication, physical and mechanical restraint as well as seclusion. We chose this primary outcome according to its frequent use in the international literature in studies on ward level: 61 out of 78 studies on the topic reduction of coercive measure chose this endpoint (7). By the calculation per bed ward of different sizes become comparable. We are using aggregated information derived from routine data of the wards. No personal data is collected.

Secondary outcome will be cumulative duration of freedom-restrictive measures (seclusion, restraint) per bed and year (in hours) as well as the change before and after the intervention for each ward of the waiting list group (waiting list period vs. intervention period).

Important variables to be controlled for will be

status of implementation at the first visit (measured with a Likert scale, see next par).number of aggressive incidents per bed and year (measurement see next par).staffing levelspercentage of involuntary admissions

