### Instruments

At the beginning of the trial, a joint evaluation by study staff and the ward team will be carried out for each of the 12 recommendations on a scale from 0 (= not implemented at all) to 9 (= fully implemented). This weighting is realized by with a Likert scale with typical anchor examples for each recommendation for the scores 0, 3, 6, and 9.

For the recording of violent incidents, the guidelines recommend the use of the SOAS-R (28). This instrument is most widespread throughout Europe and has already been introduced at many clinics in Germany. It is a well validated instrument with a score ranging from 0 to 22 (higher ratings stand for more severe incidents). In order to compensate problems of under- and over-reporting as much as possible, events will be considered only above a minimum score of 10 points. This allows both individual events and their severity to be taken into account. Furthermore, SOAS-R outcomes can be treated as continuous variables also. However, some of the participating hospitals will have introduced other, possibly less standardized instruments in their clinical practice. To avoid unwanted effects of increasing awareness in the course of the introduction of a new instrument, these hospitals will be advised to continue with their introduced instrument without any change in the practice of application.

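### Intervention wards that choose the recording or documentation recommendations can change how the primary outcome is counted, and uniform recording of coercive measures is not secured outside Baden-Württemberg

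*Protocol article*

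**What the plan says.** Outcomes defines the primary endpoint as coercive measures per bed and names its source: "We are using aggregated information derived from routine data of the wards".

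Interventions lists 12 recommendations. The first is "Implement a standardized recording of coercive measures and aggressive incidents with the possibility of regular evaluation at ward level". The second begins "Implement internal standards adapted to the guidelines regarding the indication, initiation, review, documentation, and debriefing of coercive measures". The choice belongs to the ward: "A set of up to three selected interventions will be the ward’s working focus during the interventions period". The status recorded at the first workshop feeds matching and randomisation, and the menu is presented at a second workshop. For the waiting year, Standard of Care on Control Wards says: "The participating wards should continue to apply their current strategies to prevent coercion and violence, even if they are randomized into the control group".

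Data Collection describes a legally required form, with a manual of definitions, for Baden-Württemberg. For all wards it requires that ward-level totals can be produced, and it supplies tables for delivering them. Recruitment of Wards assigns half the wards to a centre in Berlin and half to one in Ravensburg.

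Two further statements bear on recording. Interventions says "Key persons will also receive advice on collecting and delivering data", without naming an arm. Instruments asks hospitals that use their own tool for violent incidents to keep it unchanged, with the reason "To avoid unwanted effects of increasing awareness in the course of the introduction of a new instrument".

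**The concern.** Two of the selectable recommendations act on the records from which the primary outcome is read. An intervention ward that takes up either one may record more of the same events, or define them differently, from a point after the baseline count. Its matched control ward is not offered that change until the waiting year is over.

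If the change makes recording more complete, the intervention ward's count rises for reasons unrelated to how often coercion is used. A real reduction then looks smaller than it is. The protocol recognises this kind of effect for violent incidents but states no comparable protection for coercive measures. A statistical analysis plan could not repair it, because events that were never recorded cannot be recovered at analysis.

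**Working it through.** **The plan's own figure.** Inputs from Sample Size: paired two-sided t-test, 5% level, effect size 0.6, 24 pairs. With the noncentral t distribution, df = 23 and noncentrality 0.6 × √24 = 2.94, power is 80.4% (23 pairs give 78.5%). Adding 5% to 10% for the Wilcoxon test gives 24 × 1.05 = 25.2 to 24 × 1.10 = 26.4, hence 26 pairs. Simulated Wilcoxon power with 26 pairs and normal differences is 81.8%. The figure reproduces. It presupposes equal recording in both arms.

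**Bias in the rate ratio.** Let k be follow-up completeness divided by baseline completeness on an affected ward, and f the share of intervention wards affected. If affected wards have the same average rate as the others:

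observed ratio = true ratio × [1 + f × (k − 1)]

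Neither k nor f is in the protocol; both are assumed here.

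- Completeness 80% to 95%: k = 0.95/0.80 = 1.1875.
- Completeness 90% to 100%: k = 1.00/0.90 = 1.111.

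| True ratio 0.80 | f = 0.25 | f = 0.50 | f = 1 |
|---|---|---|---|
| k = 1.1875 | 0.84 | 0.875 | 0.95 |
| k = 1.111 | 0.82 | 0.84 | 0.89 |

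For example, 0.80 × (1 + 0.25 × 0.1875) = 0.8375. To hide the whole effect, k would have to be 1.25 with all intervention wards affected, 1.50 with half, or 2.0 with a quarter.

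**What share is plausible.** If each ward chose three of 12 evenly, recommendation 1 would be taken by 3/12 = 25%. At least one of recommendations 1 and 2 would be taken by 1 − (10 × 9 × 8)/(12 × 11 × 10) = 1 − 720/1320 = 45%. Wards choose by need, so these are reference points, not forecasts.

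**Power, as an illustration.** Take 26 pairs and log-scale paired differences, with the standard deviation set so that the true effect equals 0.6 standard deviations: |ln 0.70|/0.6 = 0.594 and |ln 0.80|/0.6 = 0.372. With k = 1.2 on affected wards, simulated Wilcoxon power is:

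| True ratio | f = 0 | f = 0.25 | f = 0.50 | f = 1 |
|---|---|---|---|---|
| 0.70 | 82% | 70% | 56% | 29% |
| 0.80 | 82% | 61% | 38% | 8% |

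**Why matching does not help.** Randomization pairs wards on baseline frequency and initial implementation score. Both are fixed before the ward selects its recommendations, so neither reflects a later change in recording.

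**Recommendation 1 beside Instruments.** Recommendation 1 offers new standardised recording of aggressive incidents as well as of coercive measures. Instruments tells hospitals with their own incident tool not to alter how they apply it. A ward in such a hospital that selects recommendation 1 may be unable to follow both. The conflict concerns aggressive incidents, which the Abstract calls the most important control variable.

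**The case against.** The case on the other side is substantial. Recommendations 1 and 2 are optional, and a ward that already records well has little reason to choose them. Every ward must be able to supply ward-level totals at entry, and each needs a baseline count before it can be matched. Sample Size states that outcome data are collected on every ward for routine reporting anyway, and all hospitals receive the same tables. Even where recording does improve, the likely bias is towards no effect, so the threat is lost power and not a false claim of benefit.

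Much of this stands, and it rules out four stronger readings that a reader might infer.

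- *Recording changes in one arm only, as a certainty.* The text supports a possible change on those intervention wards that choose the relevant items, and no more.
- *Advice on collecting data is reserved for the intervention arm.* The sentence appears under Interventions but names no arm. Control wards must deliver the same data, Recruitment of Wards promises support to participating hospitals generally, and Qualitative Analysis places key persons on every participating ward.
- *Instruments contradicts the menu on the primary outcome.* It concerns violent-incident instruments, not the recording of coercive measures.
- *An apparent ratio of 0.95 or 0.89 is what to expect.* Those values require every intervention ward to be affected.

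The direction is also not certain. Common definitions can remove over-counting, which would lower k below 1 and exaggerate a benefit.

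What the objection does not answer is comparability. Being able to produce a total shows that counts exist, not that they are equally complete or defined alike. The tables standardise what is sent, not what is written down on the ward. The legal form and manual are described for one federal state in a nationwide trial. The protocol itself scores recommendation 1 from 0 to 9 at entry and keeps it on the menu, so it allows for wards where recording is not yet fully in place.

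**Conclusion.** The point holds in limited form. Recording of the primary-outcome events can change differentially on intervention wards that choose recommendation 1 or 2, and no safeguard for uniform recording of coercive measures is stated outside Baden-Württemberg. More complete recording on those wards would partly mask a true reduction, and baseline matching cannot remove that. The secondary comparison of waiting period with intervention period is exposed in the same way.

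The size cannot be derived from the protocol. The range of about 0.84 to 0.95 for a true ratio of 0.80 rests on an assumed rise in completeness from 80% to 95% and on a quarter to all of the intervention wards being affected. Because planned power is only about 82%, partial uptake could still matter.

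The conflict between recommendation 1 and Instruments is a separate, smaller matter. It affects a control variable, and the two sections need to be reconciled.

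**What to change.** 1. Give all wards in both arms the same written definitions of coercive measures, the study tables and the data-collection advice before randomisation, or at the latest before the 12-month comparison period starts. State that the advice to key persons applies to both arms.
2. Leave the ward-level evaluation and feedback part of recommendation 1 selectable, so that its active content stays in the tested package.
3. Pre-specify an exploratory sensitivity analysis of the primary outcome that excludes pairs whose intervention ward chose recommendation 1 or 2. Say plainly that it conditions on a choice made after randomisation.
4. Reconcile recommendation 1 with the Instruments advice on incident recording.

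The cost is small: existing material is issued earlier and to everyone, and one analysis is added. The downside is some awareness effect on control wards, where the protocol already expects possible spill-over. The sensitivity analysis will be imprecise. Under even choice it would drop about 26 × 0.45 = 12 of the 26 pairs, so it can show whether the estimate shifts but cannot serve as a second test.

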**Figure 1 f1:**
[figure not shown]
SPIRIT flow chart: Timeline and study procedures.

Due to the heterogeneous initial situation of each ward need for action will have to be determined for each ward individually. To this end, research workers and ward managers will jointly evaluate the status of implementation at the first visit. Afterwards, ward staff will discuss and declare their preferred interventions. A set of up to three selected interventions will be the ward’s working focus during the interventions period. However, e.g., implementing a complex intervention such as Safewards is considered as sufficiently demanding to be selected alone. The underlying idea is that it would be unrealistic to fully implement all 12 recommendations within 12 months. Demand this would probably result in a low fidelity to the intervention. In addition, we assume that it makes little sense to require the implementation of elements of the intervention that might be viewed as unfeasible or undesirable by the staff. On the other hand, this means that the intervention will not be fully completed after the study period and cannot have unfolded its full power. Rather, implementation has to be considered as a process over several years, with the study intervention only boosting an initial period. The selection of individually fitting interventions by participating wards means that not all participants will deliver identical interventions. The qualitative interviews are intended to explore, among other things, why interventions are selected and which barriers had arisen during implementation.

### Standard of Care on Control Wards

The legal requirements (mental health laws, civil code) already require the use of coercion to be limited to a necessary minimum. The participating wards should continue to apply their current strategies to prevent coercion and violence, even if they are randomized into the control group and even if these strategies are also mentioned in the 12 interventions. New structured programs especially with external supervision to reduce coercion and violence further should not be implemented in this phase. However, control wards will be informed about the program and its possibilities and spill-over effects cannot be ruled out. To detect such effects, a second measurement of implementation status and outcomes will take place on the control wards before the beginning of the intervention after the waiting list status.

### Outcomes

The primary endpoint will be the number of coercive measures per bed and month/year for each ward (intervention wards vs. waiting list wards). This dependent variable includes forced medication, physical and mechanical restraint as well as seclusion. We chose this primary outcome according to its frequent use in the international literature in studies on ward level: 61 out of 78 studies on the topic reduction of coercive measure chose this endpoint (7). By the calculation per bed ward of different sizes become comparable. We are using aggregated information derived from routine data of the wards. No personal data is collected.

Secondary outcome will be cumulative duration of freedom-restrictive measures (seclusion, restraint) per bed and year (in hours) as well as the change before and after the intervention for each ward of the waiting list group (waiting list period vs. intervention period).

Important variables to be controlled for will be

status of implementation at the first visit (measured with a Likert scale, see next par).number of aggressive incidents per bed and year (measurement see next par).staffing levelspercentage of involuntary admissions

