## Introduction

Whether and under what circumstances the use of coercion in psychiatric treatment is justified is one of the oldest and most controversially discussed questions in psychiatry. Since psychiatric hospitals have long been assigned regulatory tasks in addition to medical ones, the discussion is caught between treatment and safety, patient rights and the rights of third parties. Today, most psychiatric and legal experts agree that coercive measures may only be used if other measures were not sufficient to avert danger from the patient or others. In 2011, 2016, and 2018, coercive measures in psychiatric care were the subject of landmark rulings by the German Federal Constitutional Court, each of which entailed significant changes to the Mental Health Laws (1–3).

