## Methods

### Study Design

This multicentre study applies a mixed-methods design. In this interventional trial, wards are randomized in a 1:1 ratio to either an intervention or a control condition (waiting list), stratified by the amount of coercive measures per bed and month/year and the implemented aspects of the guidelines to matched pairs. In addition, a waiting-list control design allows for a pre-post analysis for participating wards of the waiting list group. Furthermore, this design allows for analyzing if observer effects already lead to a reduction of coercive measures between the baseline and the start of the intervention as well as for assessing potential spill-over effects in the control group during the waiting time. After 12 months, control wards will receive the intervention. Pre-post analysis will also be done or interventions wards which provide additional data of one year of follow-up after the intervention. Moreover, a complementary qualitative trial in form of interviews with participating staff will be performed.

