### Statistical Analysis

The main outcome number of coercive measures per bed and year is evaluated by comparing the ward pairs by the paired Wilcoxon test at the significance level of 5%. Secondary outcome is also evaluated by the paired Wilcoxon test. In order to control confounding and reduce bias, the analyses are supplemented by multiple regression models (linear mixed models and/or generalized conditional logistic regression models) including possible covariates (number of admissions, average occupancy, proportion of involuntarily treated patients, average staffing levels). These analyses will be interpreted explorative. Raters will not be blinded due to the fact that control and interventions wards will be analyzed at different time points and additional analysis (pre-post comparison) are needed for the control wards.

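### The waiting-list before-after change is a tested secondary outcome in which intervention and calendar period cannot be separated

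*Protocol article*

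**What the plan says.** Under Outcomes, the protocol article names two items as secondary outcome: the cumulative duration of freedom-restrictive measures, and "the change before and after the intervention for each ward of the waiting list group (waiting list period vs. intervention period". Under Statistical Analysis, the main outcome is compared between ward pairs "by the paired Wilcoxon test at the significance level of 5" percent, and the next sentence adds: "Secondary outcome is also evaluated by the paired Wilcoxon test".

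Under Study Design, all control wards receive the intervention after 12 months. The original intervention wards are by then in follow-up after their own intervention.

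Two lists of adjustment variables are given. The one under Outcomes, introduced by "Important variables to be controlled for will be", holds implementation status at the first visit, aggressive incidents, staffing and involuntary admissions. The one under Statistical Analysis describes models "including possible covariates (number of admissions, average occupancy, proportion of involuntarily treated patients, average staffing levels". Neither list contains calendar time or period. Of these models the article says "These analyses will be interpreted explorative".

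Study Design also states that "this design allows for analyzing if observer effects already lead to a reduction of coercive measures between the baseline and the start of the intervention", and that spill-over in the control group can be assessed. Under Standard of Care on Control Wards, implementation status and outcomes are measured a second time on the control wards before their intervention starts.

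**The concern.** The test compares the same wards in two successive periods, and every one of them changes from waiting to intervention at the boundary between the periods. Anything else that differs between the periods enters the difference in full: a change in practice or recording, staffing shortages, or a slow drift in the use of coercion. A paired Wilcoxon test has no term that could absorb this.

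A small p-value for this outcome could thus arise without any intervention effect, and a real effect could be hidden. A related difficulty affects the observer-effect statement in Study Design. Observer effects, spill-over and secular drift all act on the same counts, in the same wards, over the same months, so the change in counts alone cannot show which of them occurred.

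**Working it through.** **Number of wards.** The Sample Size section gives 24 pairs for a paired two-sided t-test with effect size 0.6, 5% level and power above 80%. With the noncentral t distribution (n − 1 degrees of freedom, noncentrality 0.6·√n), power is 0.785 at 23 pairs and 0.804 at 24, so 24 is reproduced. Adding 5-10% gives 24 × 1.05 = 25.2 to 24 × 1.10 = 26.4, consistent with the stated 26 pairs. The waiting-list group therefore has 26 wards.

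**Identification.** Treatment state by group and year:

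| Group | Year 1 | Year 2 |
|---|---|---|
| Intervention wards | intervention | follow-up after intervention |
| Waiting-list wards | untreated | intervention |

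For a waiting-list ward, year 2 minus year 1 equals intervention effect plus period effect. No untreated cell exists in year 2, so the period effect for that year cannot be estimated separately without a further assumption. This conclusion needs no assumed figure.

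**Direction.** A secular fall adds to an apparent reduction. A secular rise subtracts from it. Spill-over during waiting lowers the year-1 value and so also shrinks the apparent reduction.

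**Size, as illustration.** The article gives neither a trend nor a within-ward variance, so every input except the 26 wards is an assumption: coefficient of variation (CV) between wards 0.8-1.2, year-to-year correlation ρ of log rates 0.70-0.85, a secular fall of 10% or 20%, no intervention effect, and a two-sided 5% level (the article states 5% for the main outcome).

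- SD of log rates: s = √ln(1 + CV²), which is 0.70 for CV 0.8 and 0.94 for CV 1.2.
- SD of the within-ward log change: s·√(2(1 − ρ)), from 0.70 × √0.30 = 0.39 to 0.94 × √0.60 = 0.73.
- Mean log change: ln(0.90) = −0.105 or ln(0.80) = −0.223.

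Share of simulated trials (20,000 per scenario) in which the paired Wilcoxon test on per-bed rates is significant:

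| CV | ρ | No drift | 10% fall | 20% fall |
|---|---|---|---|---|
| 0.8 | 0.85 | 5% | 23% | 74% |
| 0.8 | 0.70 | 5% | 14% | 46% |
| 1.2 | 0.85 | 5% | 15% | 47% |
| 1.2 | 0.70 | 5% | 10% | 27% |

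Tested on log rates, which the plan does not propose, the ranges are slightly higher: about 10-26% and 30-79%.

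**Sensitivity to the set-up.** In standardised terms, a fall of 0.1, 0.3 or 0.6 SD of the within-ward change gives 8%, 30% or 82% rejection. If all random variation is instead placed in the second year, the SD of the log ratio decides the result: a 10% fall gives 56%, 26%, 9% and 6% for SD 0.2, 0.3, 0.5 and 0.7, and a 20% fall gives more than 99%, 84%, 35% and 15%. The rates depend heavily on inputs that the article does not supply.

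**Primary comparison.** In a simulated concurrent comparison of 26 pairs, the rejection rate is 4.9% with and without a common 20% fall.

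**Would earlier data help?** If drift is linear and an equally long earlier period is available, subtracting the baseline-to-waiting change from the waiting-to-intervention change brings rejection back to about 5% (4.9% at 0.3 SD of drift, 5.2% at 0.6 SD). The correction is only as good as the assumption of linear drift.

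**The case against.** The strongest reply is that little rests on this contrast. The main result is randomised and concurrent. The article introduces the pre-post analysis as an addition to the control-group comparison, and Statistical Analysis calls it an additional analysis. The abstract names only cumulative duration as secondary, the sentence assigning the test speaks of a single secondary outcome, and the 5% level is attached to the main outcome. This limits the reach of the point. It does not remove it, because Outcomes lists the pre-post change under the same heading and no sentence exempts it from the test.

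A reader might infer three stronger things that the article does not support.

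- **That a significant pre-post result would be offered as confirmation of the randomised one.** Nothing in the text says so.
- **That a secular fall is established.** The Introduction says of the court rulings of 2011, 2016 and 2018: "each of which entailed significant changes to the Mental Health Laws". These rulings precede the ethics approval of September 2019, and the article gives no trend in counts for the trial period. Direction and size are unknown.
- **That spill-over would inflate the pre-post change.** It works towards no effect.

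On observer effects, the reply is partly right. The second measurement of implementation status on control wards helps to recognise spill-over, and the baseline-to-start comparison is the one planned look at earlier drift. Neither enters the secondary test, however, and neither separates observer effects from drift.

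Finally, model terms can be left to an analysis plan that is not shown. The choice of a before-after contrast as a secondary outcome, and of its test, is fixed in the article itself.

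**Conclusion.** The point holds for one secondary contrast. As defined and tested, the waiting-list change cannot distinguish the intervention from whatever else changed between the two periods, and none of the stated analyses repairs this. The confounding follows from the design alone. The false-positive ranges in the brief illustrate how much it could matter and rest wholly on assumed variance, correlation and trend; a secular rise or spill-over would produce a missed effect instead. The trial's main conclusion is not at risk from this source. The matter is worth correcting because the correction is cheap and changes what may be claimed from the second year.

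**What to change.** 1. In Outcomes and Statistical Analysis, move the waiting-list pre-post change from the tested secondary outcomes to descriptive or exploratory analyses, and state that it cannot separate intervention from calendar time.
2. Where an estimate is wanted, add calendar period to the mixed models already planned, using all 52 wards and all available periods. State that the year-2 estimate rests on extrapolating the trend, so the confounding is reduced under an assumption and not removed. Check first which periods can be supplied: the outcome is defined per month or year, but Data Collection secures only cumulative evaluations and describes no monthly baseline series.
3. Reword the Study Design statement so that a baseline-to-start fall on control wards is attributed to observer effects, spill-over or secular drift only as far as the re-measured implementation score supports it. A fall accompanied by a higher score points towards spill-over; a fall without one leaves observer effects and drift undistinguished.

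Cost: one secondary outcome loses its test, the outcome list of a registered trial has to be updated accordingly, and a little more modelling is needed. Randomisation, sample size and the primary analysis are unchanged.
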